# Investigating the effect of vitamin D vaginal suppository on sexual function among postmenopausal women: study protocol for a randomized controlled trial

**DOI:** 10.1186/s12905-020-00899-6

**Published:** 2020-02-18

**Keywords:** Menopause, Sexual function, Vitamin D vaginal suppository

## Abstract

**Background:**

Menopause is associated with changes in sexual function which are partly due to vaginal atrophy in response to estrogen reduction. Estrogen administration temporarily reduces the symptoms of vaginal dryness, but long-term exposure to this drug is likely to be associated with serious complications. Considering the promising results of previous studies concerning the effect of vitamin D on vaginal dryness, the proposed study will investigate the effect of vitamin D vaginal suppository on the sexual function of postmenopausal women.

**Methods:**

In a randomized, controlled clinical trial, 105 postmenopausal women will be randomly assigned to three groups receiving vitamin D vaginal suppository, placebo vaginal suppository, or control (no intervention). Vitamin D vaginal suppositories contain 1000 units of vitamin D3. The timing of the use of vitamin D vaginal suppositories and placebo suppositories will be every night in the first 2 weeks, and every other night in the following 6 weeks (8 weeks in total). The primary outcome will be the sexual function of participants which will be assessed using the Female Sexual Function Index (FSFI) before and immediately after the intervention, and at 1 and 2 months after the end of the intervention. The side effects of these suppositories will be examined as a secondary consequence of the study. Data will be analyzed using SPSS software version 25. In the case of normal distribution of data, the mean score of sexual function will be compared between the groups using a repeated measurements ANOVA. If statistical analysis leads to significant results, the post-hoc test will be used to determine the differences between the groups. Comparison of demographic and fertility characteristics of the women will be carried out using statistical tests such as chi-squares and *t*-tests. A significance level of *p* < .05 will be used for statistical analyses.

**Discussion:**

If vitamin D vaginal suppositories improve sexual function among premenopausal women with long-term effects and minimum side effects, the suppositories will be considered a safe complementary and alternative choice for alleviating sexual dysfunction among this group.

**Trial registration:**

IRCT20180704040346N1 at 2018-10-13 prospectively registered.

## Background

Menopause – as one of the critical and inevitable stages of women’s life – is the most important event during middle age. It can have a particular influence in women’s personal, cultural, social, reproductive health, and sexuality [1]. Menopause leads to many physiological changes that occur continuously and gradually, and can affect the woman’s life [2]. Menopause occurs gradually from the late third decade of life between the ages of 40 and 60 years and a mean of 51 years [1]. According to studies conducted in Iran, the range of menopausal age ranges between 46 and 52 years [3].

The climacteric phase and menopause are the periods of reductions in the production of hormones, that can affect women’s quality of life because of various complications [4]. These complications can include symptoms such as hot flushes, night sweats, palpitations, bone loss, urinary problems, and vaginal dryness [5]. Vaginal dryness (as one of the problems caused by the reduction of estrogen production) is due to thinning of the endometrial tissue and increase of pH, that cause local itching, an increase in the incidence of vaginal infection, and vaginal structural weakness. In addition, dyspareunia can cause sexual dysfunction and loss of sexual desire during menopause [6]. Vaginal atrophy, after hot flushes, is the second most common complication and is the worst complication of menopause [4]. Reducing estrogen levels through causing fractures in collagen and elastin fibers in the vagina causes vaginal atrophy. From a cytomorphological aspect, parabasal cells are increased and intermediate and superficial cells are decreased [7].

Problems with vaginal atrophy are clinically manifested 4–5 years after the beginning of menopause [8]. Vulvovaginal atrophy lead to vaginal dryness, irritation, soreness, and consequently dyspareunia [9, 10]. Approximately one-third of postmenopausal women report painful intercourse (dyspareunia), lack of moisture, and decreased lubrication [11]. Common symptoms of atrophy include vaginal dryness, burning, post-coital bleeding, and pain [12]. In clinical examination, symptoms such as being pale, the reduction of transverse vaginal folds (roga), petechiae, reduced elasticity, and dryness confirms the presence of atrophy [5]. Vaginal atrophy is one of the causes of sexual problems, and is one of the most important complaints among women during the menopause, but despite many advances in the prevention and treatment of menopausal complications, sexual problems are underestimated [13].

One of the therapeutic methods for improving the symptoms of vaginal atrophy and dyspareunia in postmenopausal women is estrogen therapy [14]. Estrogen improves the mucosa, and increases elasticity and blood flow to vulva and vaginal area. It also increases the sensory threshold of the vulva region and vagina, increases sexual pleasure, and improves arousal [15]. Since estrogen deficiency is the main cause of vaginal atrophy, estrogen therapy after menopause is the most rational choice of treatment. Systemic estrogen therapy is the gold standard in slowing down and/or preventing early genital atrophy, but maintaining its effect requires continuous treatment [2]. The other initial and preferable and choice in treating genitourinary syndrome of menopausal women is ultralow-dose topical estriol [16]. Overall, due to the potential risks of postmenopausal systemic hormone replacement therapy, estrogen replacement therapy may not be acceptable by many women [8]. Concerns about the complications of estrogen therapy, including cardiovascular events, thromboembolism, breast cancer, and endometrial hyperplasia are the most important reasons for the low acceptance of synthetic estrogen therapy [17]. In addition to the aforementioned concerns, a considerable proportion of menopausal women experience some type of chronic disease such as diabetes, cardiovascular disease, dyslipidemia, and asthma [18], so they are not good candidates when administering many kinds of hormone therapy. Regarding these issues, there is an increasing tendency to utilize alternative treatments for relieving menopausal symptoms [17].

Vitamin D is one of the essential substances in metabolic and physiological processes in the body [19]. Recent literature has reported the role of low level of vitamin D in many pathological conditions including cardiovascular disease, type 2 diabetes mellitus, metabolic syndrome, cancer, and increased mortality, as well as its role in calcium and bone metabolism [20]. Recent research has also shown that vitamin D3 may be useful in preventing vaginal atrophy. Vitamin D3 may play a role in regulating the growth and differentiation of the vaginal epithelium. Costantino’s research found that taking vitamin D3 can help prevent osteoporosis and eliminate vaginal discomfort after the menopause [6]. Vitale et al. (2018) reported after a randomized, placebo-controlled trial, that oral supplements of vitamin D in combination with isoflavones, calcium, and inulin significantly improved the sexual function of menopausal women [21]. In a cross-sectional study, Yildirmal et al. (2004) showed that the use of vitamin D supplements was effective in the maturation of vaginal cells [22]. Also, a clinical trial by Zainlugl et al. (2007) showed that in postmenopausal women with osteoporosis, Raloxifene and vitamin D supplementation significantly reduced vaginal dryness and pH [23].

Vitamin D3 can be absorbed in the vagina by applying a vaginal suppository [11]. The results of a clinical trial study by Rad et al. (2014) on postmenopausal women in Ahwaz (Iran) showed that vitamin D suppositories could experimentally (according to the results of the participants’ Pap smear) improve dryness and cell proliferation of the vaginal mucosa among postmenopausal women [24]. The possible mechanism for the effect of vitamin D on the vagina is due to the presence of intracellular receptors of this vitamin in the basal and parabasal cellular layer in the vaginal tissue. Because of these receptors in the vagina, vitamin D can play an important role in regulating and increasing the proliferation of epithelium cells in vagina [25, 26]. However, vitamin D receptors change during the menstrual cycle, which means that by stopping ovarian activity, the number of receptors are decreased [27].

The results of experiments in rats have shown that ovarian harvesting results in the loss of vitamin D receptors. It has been shown that the use of vitamin D in mice increases the number of vitamin D receptors and the coating tissue becomes better integrated [25, 28]. The biological effect of vitamin D is applied via the nucleus receptors. These receptors are found in several tissues such as the liver, kidney, thyroid, adrenal gland, gastrointestinal tract, breast, and skin. Together, vitamin D and its receptors can negatively or positively affect the transcription of genes. Therefore, vitamin D is effective as a precursor in the differentiation and amplification of keratinocytes and restoring mucosal tissue of the vagina [29]. In addition, research has shown that squamous cell differentiation takes place in several steps, each of which is controlled by specific genes [30, 31].

The present review of existing literature shows that there are a few studies on the effect of vitamin D on vaginal atrophy and the efficacy of treatment has mostly been investigated under laboratory conditions using the Pap smear. No study has investigated the effect of vitamin D on clinical manifestations such as sexual function of postmenopausal women. On the other hand, the results of available studies have not been consistent. For example, Yildirmal et al. (2004) reported that the symptoms of vaginal atrophy in both Vitamin D treatment and control groups and that there were no significant differences between the groups [22]. On the other hand, Rad et al. (2014) reported significant differences after the end of 8 weeks among an intervention group with vitamin D vaginal suppository compared to the control group [24]. In another study, vitamin D was also used in combination with other treatments such as topical steroids and raloxifene [23], but the study did not provide conclusive evidence concerning the efficacy of vitamin D on vaginal atrophy. Other limitations of these studies were that some of them did not use a control group, random allocation, and blindness, and the duration of the follow-up of patients was short. Therefore, since there is no previous study concerning the clinical effect of the use vitamin D on women’s sexual function, and considering the strengths and weaknesses of previous studies, the proposed study is designed to evaluate the effect of vitamin D3 vaginal suppositories on the sexual function of postmenopausal women.

### Goals and hypotheses

The present study is based on the hypothesis that vitamin D vaginal suppository will have an effect on the sexual function of postmenopausal women by improving the symptoms of vaginal atrophy. As explained above, the possible mechanism might be due to the regulating and proliferative function of intracellular receptors of vitamin D in the basal and parabasal cellular layer in the epithelial tissue of the vagina [25–27]. The results of experiments in rats as well as a few approved clinical trials demonstrate that the use of vitamin D increases the number of vitamin D receptors and that the coating tissue is better integrated [24, 25, 28]. With this background in mind, the specific objectives of the proposed study include the:
Comparison of sexual function in postmenopausal women within intervention, placebo, and control group, before, immediately after, and one and 2 months after the intervention;Comparison of sexual function in postmenopausal women between the intervention, placebo, and control groups immediately after, and one and 2 months after the intervention.

## Methods/ design

### Research setting and design

The proposed study is designed as a randomized clinical trial with two parallel control groups of placebo and no intervention. Participants will be married women between the ages of 45 and 65 years referred to comprehensive health centers in the city of Buin Zahra, who meet the inclusion criteria. Buin Zahra is one of the cities of Qazvin province. This city consists of four areas (central, Dashtabi, Ramand and Shal). Figure 1 provide study flowchart.

**Fig. 1 Fig1:**
[figure not shown]
Consort diagram of study

### Participants

All postmenopausal women aged 45- to 65-years-old living in Buin Zahra district will be invited to participate in the study via their health care providers. Eligible participants from 25 urban and rural comprehensive health center affiliated to abovementioned four districts of Buin Zahra will be included in this study. The exclusion criteria will be (i) the presence of other endocrine diseases such as Cushing disease, diabetes, etc., (ii) using other vaginal drugs, (iii) having moderate to severe vaginal infection, (iv) undergoing hormone therapy, (v) having a stressful experience during the past 3 months, (vi) experiencing pelvic abnormalities, (vii) having recent surgery, and (viii) unwillingness to participate in the study. Also excluded will be those with absolute contraindications of vitamin D supplement including sarcoidosis, hyperphosphatemia, hypercalcemia, hyper-vitamin D levels, arteriosclerosis, kidney stones, and kidney disease that causes a reduction in kidney function.

### Sample size estimation

According to previous study by Çayan et al. [32], considering α = 0.05, power = 80%, moderate effect size 0f 0.6, the sample size for the research study was estimated to be 25 people for each group. Considering the attritional loss of 40% of the samples in the research process, the sample size for each group was calculated to be 35 people. The sample size calculation was performed according to primary outcome of study.

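### The printed inputs (alpha 0.05, 80% power, effect size 0.6) do not give 25 per group for a standard between-group comparison; 25 is recovered only with assumptions the protocol does not state

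*Protocol article*

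**What the plan says.** Protocol article, Sample size estimation: drawing on a cited earlier study, and with alpha 0.05, the section gives "power = 80%, moderate effect size 0f 0.6, the sample size for the research study was estimated to be 25 people for each group". After an allowance for 40% attrition, "the sample size for each group was calculated to be 35 people", which matches the abstract's Methods: "105 postmenopausal women will be randomly assigned to three groups". The section says the calculation was done for the primary outcome.

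That outcome is the Female Sexual Function Index (Primary outcome measurements). It is measured before treatment, at the end of treatment, and one and two months later. Goals and hypotheses lists a within-group comparison over all four times and a between-group comparison at the three post-treatment times. Data management and analysis plans a repeated-measures ANOVA between the three groups, followed by a post-hoc test if it is significant.

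No section states the test behind the figure of 25, whether 0.6 is Cohen's d or Cohen's f, whether alpha is one- or two-sided, or what correlation between visits was assumed.

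**The concern.** A reader who puts the three printed inputs into the usual two-group formula gets 45, not 25. The word moderate points to Cohen's d: as Cohen's f, 0.6 would be a large effect. The article therefore prints inputs and a result that do not belong together under the simplest reading of a between-group comparison.

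The power statement tells readers how to interpret a null result. If the trial is taken to have 80% power at 0.6 and vitamin D does not beat placebo, that will be read as fair evidence against a moderate effect. If power for that contrast is well below 80%, the reading is too strong.

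**Working it through.** **Inputs.** From Sample size estimation: alpha 0.05, power 80%, effect size 0.6, 25 per group, 40% attrition, 35 per group. From the abstract and Goals and hypotheses: three groups, three post-treatment visits. Assumed, because not stated: two-sided testing (one-sided also tried), equal variances, and a common correlation ρ between visits, ranged over 0.3, 0.5 and 0.7.

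**Step 1: try to reproduce 25 with a two-group comparison, d = 0.6.**
Normal approximation: n = 2(z₀.₉₇₅ + z₀.₈₀)²/d² = 2(1.960 + 0.842)²/0.36 = 43.6, so 44. The exact noncentral t gives 45. One-sided, the exact figure is 36. With a Bonferroni correction for three pairs it is 60. None gives 25.

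**Step 2: power of that test at the relevant sizes.**
At n = 25 the noncentrality is 0.6 × √(25/2) = 2.121, against a critical t (48 df) of 2.011.

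| Analysed per group | Power at d = 0.6 | d detectable with 80% power |
|---|---|---|
| 21 (35 × 0.6) | 47.5% | 0.89 |
| 25 | 54.7% | 0.81 |
| 35 (no loss) | 69.7% | 0.68 |

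One-sided power at 25 is 67.2%.

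**Step 3: other readings, n per group for 80% power.**

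| Reading | n per group | Power at 25 |
|---|---|---|
| One-way ANOVA, f = 0.6 | 10 | 99.7% |
| One-way ANOVA, f = 0.3 (= d/2) | 37 | 61.9% |
| One-way ANOVA, one arm shifted 0.6 SD (f = 0.283) | 42 | 56.5% |
| Paired t within one group, standardised change 0.6 | 24 | 82% |
| Repeated-measures between-group factor, f = 0.3, three visits, ρ = 0.5 | 25 | 80.3% |
| Same, ρ = 0.3 | 21 | 88.7% |
| Same, ρ = 0.7 | 30 | 72.3% |

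For the repeated-measures factor the noncentrality is λ = f²·N·m/(1 + (m − 1)ρ). With N = 75, m = 3, ρ = 0.5 and f = 0.3, λ = 0.09 × 75 × 3/2 = 10.125. The F test on 2 and 72 df then has 80.3% power. So 25 can be reproduced this way.

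**Step 4: is f = 0.3 consistent with an effect size of 0.6?**
The conversion f = d/2 holds for two groups. With three equal groups whose means differ by at most 0.6 SD, f is largest when two arms coincide and the third is 0.6 away: f = 0.6 × √2/3 = 0.283. Then λ = 0.08 × 75 × 3/2 = 9.0, power at 25 is 75%, and 28 per group are needed at ρ = 0.5 (23 at ρ = 0.3, 34 at ρ = 0.7).

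**Step 5: vitamin D versus placebo on the mean of the three post-treatment visits.**
The variance of the mean of three visits is (1 + 2ρ)/3 of a single visit's, so the effective standardised difference is 0.6/√((1 + 2ρ)/3). The same noncentral t then gives:

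| ρ | Effective d | Power at 25 | Power at 21 |
|---|---|---|---|
| 0.3 | 0.822 | 81% | 74% |
| 0.5 | 0.735 | 72% | 64% |
| 0.7 | 0.671 | 64% | 56% |

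These figures carry no multiplicity correction for the post-hoc step.

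**The case against.** The strongest reply is that the protocol does not plan a single-visit t-test. It plans a repeated-measures ANOVA, and its between-group objective covers exactly three post-treatment visits. For that analysis f = 0.3 and a correlation of 0.5 return the protocol's own number, with no need to suppose that the arms differ at baseline. A paired test, which suits the within-group objective, gives 24. The effect size comes from a cited study that is not at hand, and a condensed article may leave the test and correlation to a fuller document.

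Much of this stands. A reader might infer from Step 2 that the trial's true power is 55%, or that 45 per group are definitely required. The documents do not support that: 55% belongs to a single-visit, unadjusted two-group comparison, which is not the planned main analysis. A reader might also infer that a repeated-measures calculation reaches about 25 only by treating baseline as a visit at which the arms differ. That is wrong too, since the three post-treatment visits alone give 25.

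The reply still does not rescue the printed statement. The repeated-measures route needs a correlation that the protocol does not give, and an f that three arms within 0.6 SD of each other cannot reach. The paired test sizes change within one group, not the randomised comparison. Brevity may excuse an unstated correlation, but the article chose to print specific inputs and a specific result, and no standard between-group test using only those inputs connects them.

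**Conclusion.** The point holds in this form: the printed inputs do not yield 25 per group for a standard between-group comparison of the primary outcome, and the 80% claim depends on unstated assumptions. For a single-visit, unadjusted two-group comparison at d = 0.6, 45 per group are needed and 25 give about 55% power. For the mean of the three post-treatment visits, power for vitamin D versus placebo at 25 per group runs from about 64% to 81% as the assumed correlation falls from 0.7 to 0.3, and reaches 80% only near the low end. No single figure can be given as the power of the planned analysis, because the documents fix neither the index nor the correlation.

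The results assume that 0.6 is Cohen's d, two-sided alpha 0.05, equal group sizes, equal variances and a common correlation between visits. The figures at 21 per group apply the protocol's own 40% loss to 35 (35 × 0.6 = 21). Whether 35 is the right inflation of 25 is a separate matter.

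**What to change.** Keep 105 women. Replace the claim of 80% power at 0.6 with 25 per group by a statement that names:

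- the contrast (vitamin D versus placebo);
- the analysis the figure refers to, and whether it is two-sided;
- the effect-size index (Cohen's d);
- the assumed correlation between visits, with a range if it is not known;
- the resulting power or detectable effect.

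If the figure is for a single-visit unadjusted comparison, state about 55% power at 25 analysed and 48% at 21, or a detectable d of about 0.81 and 0.89. If it is for the mean of the three post-treatment visits, state about 64% to 81% at 25 analysed for correlations from 0.7 down to 0.3. If 25 came from a repeated-measures or paired calculation, say so and give its inputs.

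This changes wording only: no change to recruitment, visits or treatment. The cost is a less favourable stated power.

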### Recruitment

To recruit the participants, eligible individuals will be selected on the basis of information in the health records of the comprehensive health centers in the city of Buin Zahra. A total of 105 eligible individuals will be invited to participate in the study. After screening the eligible individuals based on their health records, they will be called and invited for a visit in their comprehensive health care center. When they come for the screening visit, they will interviewed to assess eligibility criteria, introducing the project, its’ aim, their autonomy to participate in the study, confidentiality and anonymity of collected data. After signing the written consent, they will be randomized to study groups.

### Randomization

The participants will be randomly assigned into the study groups. Random allocation will be carried out using the simple randomization method, and assignment sequences will be written on paper before the start of the research as either A (suppository of vitamin D3 group), B (placebo suppository group), and C (control group without intervention). Randomization will be performed using random allocation software. The type of intervention will be written in accordance with the assignment sequence and will be enclosed within the opaque envelopes. Questionnaires will be also encoded in sequence. In this case, the questionnaire with the same code will be completed for the person receiving the code 1 intervention.

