### Blinding

Due to having a control group which receives no intervention, blinding cannot be performed for all groups. But in try to blind intervention and placebo controlled group, vitamin suppositories and placebo suppositories will have the same color and shape and will coded as A and B by a pharmacologist not involved in the research team. The researchers will receive the suppositories with codes and will not know what A and B stands for with respect to the suppositories. Finally, after collecting questionnaires and analyzing data using SPSS version 25 software, the codes that belong to the groups will be determined.

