### Intervention program and patient education

During the first visit, the vaginal suppositories (without identifying the type of suppository, only having an identifier code inside the appropriate envelopes) will be given to the participant. The method and duration of use, as well as the follow-up time will be taught by the researcher to each participant. A phone number will be provided to ensure that the supplements are properly used and participants will reminded to keep track of the follow-up time. The researcher’s phone number will be shared with the participants to contact them if they have any questions about how to use the suppositories and/or if they experience any problems or signs of burning and itching following the use of the suppositories. As noted above, the total time period to take the suppositories for each postmenopausal woman will be 8 weeks, during which the investigator will monitor the use of the suppositories in the women by telephone or text-messaging (based on the convenience of the participant).

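### The Randomization, Blinding and patient-education sections contradict each other on what the letters A and B mean and what the envelopes hold, which puts the researchers' blinding for vitamin D versus placebo at risk

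*Protocol article*

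**What the plan says.** Three sections of the protocol article bear on this.

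- **Randomization.** The assignment sequences are "written on paper before the start of the research as either A (suppository of vitamin D3 group), B (placebo suppository group", with C for the group that receives nothing. The section goes on: "The type of intervention will be written in accordance with the assignment sequence and will be enclosed within the opaque envelopes". Questionnaires are numbered in the same sequence.
- **Blinding.** The no-intervention arm is acknowledged to be open. For the other two arms, "vitamin suppositories and placebo suppositories will have the same color and shape", and they "will coded as A and B by a pharmacologist not involved in the research team". Then: "The researchers will receive the suppositories with codes and will not know what A and B stands for with respect to the suppositories". The code is to be broken last: "after collecting questionnaires and analyzing data using SPSS version 25 software, the codes that belong to the groups will be determined".
- **Intervention program and patient education.** At the first visit the woman is given her suppositories "without identifying the type of suppository, only having an identifier code inside the appropriate envelopes".

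The article does not say who prepares, keeps or opens the list and the envelopes. It does not say that the letters on the list differ from those on the suppositories. Nor does it say whether the envelopes in the first and third sections are the same ones.

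**The concern.** One section publishes the meaning of A and B in advance. The next treats that meaning as unknown to the researchers until the data have been analysed. If the letters are the same, the key to the blind is printed in the protocol that the research team works from.

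This matters because of what the researchers do. They teach each woman how to use the suppositories, are her contact for problems, and follow her use by telephone or text over the 8 weeks. The primary outcome, the Female Sexual Function Index (FSFI), is self-reported, so a researcher who knows the arm could pass on expectations through that contact. The Intervention section also places the baseline FSFI after random allocation, so knowledge of the arm could touch the baseline as well as the follow-up scores. An analysis on data labelled A and B is blinded only if the analyst cannot read those labels.

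Since the untreated arm is open, vitamin D versus placebo is the only contrast in the trial that blinding can protect.

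**Working it through.** No power, sample-size or test calculation is involved. The check is a comparison of the texts, followed by one count.

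**Step 1. Set the statements side by side.**

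| Item | Randomization | Blinding | Patient education |
|---|---|---|---|
| Meaning of A and B | Fixed before the study: vitamin D3 and placebo | Not known to the researchers until after analysis | Not mentioned |
| Label on the suppositories | Not mentioned | A or B | An identifier code |
| Envelope content | Type of intervention | Not mentioned | Identifier code, type not identified |
| Who holds the key | Not stated | The pharmacologist does the coding; custody of the list not stated | Not stated |

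**Step 2. Ask under which reading all the statements could be true.**

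1. *List letters and suppository letters are the same.* The key is then the one in the Randomization section, and anyone who has read it can identify both products. The Blinding section's statement fails.
2. *The pharmacologist assigns A and B to the products independently of the list.* A woman listed under A as vitamin D3 can be given the right pack only by someone who knows which pack letter is vitamin D3. If a researcher does the matching, that researcher is unblinded. If someone outside the team does it, the blind survives, but the article describes no such step.
3. *The bracketed meanings are for the reader only, and the envelopes carry a neutral code.* The blind survives, but then the sentence that puts the type of intervention in the envelopes is wrong as it stands.

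No reading keeps every sentence intact without adding a step that the article does not describe.

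**Step 3. Ask who is affected.** The contradiction concerns the researchers and the analysis. Participants are covered separately by the matched appearance of the suppositories and by coded packs.

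**Step 4. Count how many women depend on one key.** The Sample size estimation section plans 35 women per group, and two groups receive suppositories: 2 × 35 = 70 of the 105. With one letter per arm, learning the content of one woman's pack reveals it for everyone with that letter, about 35. As there are only two letters, the other arm follows by elimination, so about 70 in all. Simple randomization does not guarantee exactly 35 per arm, so 70 is the planned figure. It measures exposure of the code, not bias.

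**The case against.** The strongest reply is that nothing shows the blind to be lost. The coding is given to a pharmacologist outside the team, and the article says outright that the researchers do not know the meaning of the letters. The brackets in the Randomization section may only tell the reader which arms exist. The type in the envelope can be read, with the patient-education section, as a coded type. The sequential questionnaire codes suggest that individual codes may exist beside the letters. Custody of the list is a detail that a condensed article commonly leaves to the full protocol.

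Much of this stands. A reader might infer that the printed key removes the blind on the trial's primary comparison. The article does not support that, for three reasons:

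- It does not say who holds the list, or who opens the envelopes and when.
- The women who complete the FSFI remain masked by identical appearance and coded packs, unless they see the key or the envelope content, or staff convey it.
- It names a primary outcome but no primary pairwise comparison; its objectives compare all three groups.

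What does not stand is the suggestion that this is only missing detail. Silence about the custodian alone would be no finding in an article. Here, however, the article states one procedure that gives the letters a meaning and encloses the treatment type, and another that depends on that meaning being hidden.

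That a two-letter code is fragile is a separate design point. It would hold even if the contradiction were resolved in the benign direction.

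**Conclusion.** The contradiction between the three sections is real and needs no assumption beyond the text. Its consequence is a risk: followed as written, the procedure can unmask the researchers who teach and monitor the women, and can undo the planned blinded analysis, for vitamin D versus placebo. Whether this would happen depends on who holds the list and what the envelopes actually show, which the article leaves open. Any effect on the participants' answers would be indirect, through contact with staff.

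The arm-wide letter makes a single disclosure costly, since it would expose all of the roughly 70 women planned for the two suppository arms. The direction and size of any resulting bias in FSFI scores cannot be derived from the article.

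**What to change.** Reconcile the Randomization, Blinding and patient-education sections so that they describe one procedure:

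- The pharmacologist outside the team alone holds the allocation list and the key, and releases the key only once the primary analysis is complete.
- Each woman in a suppository arm receives a pack with its own number.
- Each envelope shows only that pack number or the word 'control', never the content and never a letter shared by a whole arm.
- The analysis dataset uses group codes unrelated to the A and B defined in the Randomization section.

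The cost is the relabelling of about 70 packs, one list kept by the pharmacologist who already does the coding, and a few rewritten sentences. Sample size, visits and outcome measures are unchanged.
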